### Statistical analyses

In accordance with the research questions, statistical analyses will be conducted to determine whether the groups differ in changes over time in proximal, distal as well as secondary outcomes. Statistical significance will be set at the 5% level (two-tailed). To adjust for company and clustering, analyses will be performed using multilevel modelling. The models will include allocated group (reference group = control group) and baseline values. Both crude models and models adjusted for potential confounders will be determined. Potential confounders will be defined a priori based on the findings from the larger research project. Separate models will be made for the different outcomes regarding physical activity, sedentary behavior, mental health and cognition. All analyses will be performed using both per protocol and intention to treat approaches, were intention to treat is defined as persons attending at least 3 out of 5 counselling sessions.

Moderator analysis will examine whether intervention effects differ across individual (e.g. age, gender and education). Mediator analyses will test whether individual and organizational factors, described under working mechanisms, mediated the intervention effects.

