### Research questions

For inactive and sedentary office workers, does a multi-component intervention to promote physical activity or reduce sedentary behavior lead to more favorable physical activity and sedentary behavior?Do favorable changes in physical activity or sedentary behavior result in better mental health and cognition, on the short and long term?

The primary hypothesis is that the multi-component interventions will favorably change office-workers physical activity or sedentary behavior as compared to the waiting list control group at 6 months. The secondary hypothesis is that these changes in physical activity patterns will in turn have positive longer term effects on mental health and cognition.

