### Design

The design is a 3-armed, clustered randomized controlled trial with waiting list control group, see Fig. 1. This 24-months study includes 5 assessment points. The outcomes of the randomized controlled trial are based on the first two measurement points. After that, the study continues as a cohort study with long term follow-up measurements of up to 1.5 years after the end of the intervention.

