### Sample size

Sample size was calculated in three steps [67]:i.Sample size based on an individualized randomized controlled trialii.Corrected for the design effect, taking into account the clusteringiii.Corrected for unavailable data

The sample size calculation was based on 1 follow-up measurement, with a power of 80% and significance level of 0.05, corrected for 3 groups (0.05/3 = 0.017).

The design effect was 1.77. This was determined, assuming that the proportion of variance accounted for by between cluster variations was 0.05 [68]. Furthermore, we corrected for unequal clusters, assuming an average cluster size of 14 with a standard deviation of 5.83.

Unavailable data were assumed by correcting for the drop out of 3 clusters, with an average cluster size of 14 per group and for unavailability of data (missing, individual drop-outs) for 20% of participants.

For the remaining input of the sample size calculations, data were used from subproject 1 of the larger research project (as described earlier).

Using these input, estimated needed sample sizes are the following:Physical activity, moderate to vigorous physical activity, meeting the guidelines

Proportion of participants meeting guidelines in control group: 30%.

Estimated proportion of participants meeting guidelines in intervention groups: 60%.i.*Sample size based on individualized randomization:* 52 per groupii.*Corrected for design effect:* 92 per groupiii.*Corrected for unavailable data:* 125 per groupSedentary behavior, total sedentary behavior, in hrs/day

Difference in mean value between groups: 1 h/day.

Standard deviation: 1.4 h/day.i.*Sample size based on individualized randomization:* 41 per groupii.*Corrected for design effect:* 72 per groupiii.*Corrected for unavailable data:* 101 per groupMental health, stress, single item [24]

Proportion of participants with stress complaints in control group: 26%.

Estimated proportion of participants with stress complaints in intervention groups: 5%.i.*Sample size based on individualized randomization:* 57 per groupii.*Corrected for design effect:* 100 per groupiii.*Corrected for unavailable data:* 134 per groupCognition, stroop test (in seconds)

Difference in mean value between groups: 7 s.

Standard deviation: 9.85 s.i.*Sample size based on individualized randomization:* 41 per groupii.*Corrected for design effect:* 73 per groupiii.*Corrected for unavailable data:* 102 per group

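### The sample size uses 0.017 to allow for three groups, but the analysis section tests at 5% with no correction for the group comparisons

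*Protocol article*

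**What the plan says.** The trial has three arms: a physical activity intervention, a sedentary behavior intervention and a waiting list (Design: "The design is a 3-armed, clustered randomized controlled trial with waiting list control group").

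The Sample size section computes a number per group for four outcomes: guideline attainment, sedentary hours, a stress item and the Stroop test. It does so "with a power of 80% and significance level of 0.05, corrected for 3 groups (0.05/3 = 0.017").

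The Statistical analyses section covers proximal, distal and secondary outcomes and gives one threshold: "Statistical significance will be set at the 5% level (two-tailed"). On the model it says "The models will include allocated group (reference group = control group) and baseline values", which yields two contrasts with control for each outcome. It adds that "Separate models will be made for the different outcomes regarding physical activity, sedentary behavior, mental health and cognition". It mentions neither the 0.017 level nor any other procedure for the group comparisons.

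**The concern.** The two sections give different levels for the same comparisons. The design treats the three-group comparison as needing a stricter level and asks for more participants to support it. The decision rule then states an unadjusted 5%. A group difference with p between 0.017 and 0.05 would be called significant under one section and not under the other.

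What is at stake is the claim that can be made for each outcome at 6 months. If 5% is applied to every contrast with control, the chance of at least one false claim on an outcome is well above the 5% that the sizing was set up to hold.

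**Working it through.** **Inputs**, all from the Sample size section unless noted:

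- Power 80%; level 0.05/3.
- Guideline attainment 30% v 60%; stress 26% v 5%.
- Sedentary time: difference 1 h/day, SD 1.4. Stroop: difference 7 s, SD 9.85.
- Design effect 1.77; 20% unavailable data; allowance for lost clusters of average size 14.
- Target of 110 per arm (Abstract, Methods).

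**Step 1. Which level was used for sizing?** With the two-sided normal approximation and z_β = 0.842:

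- Means: n = 2·SD²·(z_α/2 + z_β)²/Δ².
- Proportions: n = [p₁(1−p₁) + p₂(1−p₂)]·(z_α/2 + z_β)²/(p₁−p₂)².

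At α = 0.05/3, (2.394 + 0.842)² = 10.47. At α = 0.05, (1.960 + 0.842)² = 7.85.

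| Outcome | Stated n | n at 0.05/3 | n at 0.017 | n at 0.05 |
|---|---|---|---|---|
| Guideline attainment | 52 | 52.3 | 52.1 | 39.2 |
| Sedentary time | 41 | 41.0 | 40.9 | 30.8 |
| Stress | 57 | 57.0 | 56.7 | 42.7 |
| Stroop | 41 | 41.5 | 41.3 | 31.1 |

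Example, guideline attainment: (0.21 + 0.24)·10.47/0.09 = 52.3. All four stated figures agree with the corrected level and none with 5%.

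**Step 2. Familywise error for one outcome.** Take three equal arms, no true differences, and test statistics (x_i − x_j)/√2 from independent standard normal x. The two contrasts with control then have correlation 0.5. Simulation with 2 million draws gives:

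| Level per comparison | Two contrasts with control | All three pairwise |
|---|---|---|
| 0.05 | 9.0% | 12.2% |
| 0.05/3 | 3.1% | 4.4% |

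Two contrasts is the base case, because the model takes control as its reference. The three-way figure applies only if the two interventions are also compared.

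**Step 3. What 0.017 costs at the recruitment target.** The stated clustered numbers (92, 72, 100, 73), multiplied by 1.2 plus 14, give 124.4, 100.4, 134.0 and 101.6. Rounded up, these are the stated 125, 101, 134 and 102. The protocol does not write this formula out, so it is an assumption that fits its figures. Reversed for 110 per arm: (110 − 14)/1.2 = 80, and 80/1.77 = 45.2 effective per arm.

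Power = Φ(|Δ|/SE − z_α/2), where SE² = 2·SD²/45.2 for means and [p₁(1−p₁) + p₂(1−p₂)]/45.2 for proportions:

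| Outcome | Needed per arm | Power at 0.05/3 | Power at 0.05 |
|---|---|---|---|
| Guideline attainment | 125 | 73% | 85% |
| Sedentary time | 101 | 84% | 92% |
| Stress | 134 | 69% | 82% |
| Stroop | 102 | 84% | 92% |

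**The case against.** The best defence is that 5% in the analysis section is the overall level. The Sample size section also starts from 0.05 before correcting it, and an unseen analysis plan may supply the procedure. An article may fairly leave the choice of multiplicity procedure to that plan. This article, however, goes further than staying silent: it states a threshold that differs from the one used for sizing and gives nothing to link them. That discrepancy stands, although nothing shows that the sponsor intends uncorrected testing.

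It is also fair to say that adjustment for two distinct interventions sharing one control is debated. A sponsor may argue for unadjusted testing, but this one adopted the correction when setting the sample size, so dropping it needs a reason.

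Two stronger readings are tempting, and the document does not support them.

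- A reader might count every activity summary, mental health measure and cognitive test and conclude that the sizing's protection is lost across all of them. Dividing by three covers only the group comparisons within one outcome. It never extended across outcomes, so error accumulated over outcomes is a different question.
- A reader might infer from the primary hypothesis ("multi-component interventions will favorably change office-workers physical activity or sedentary behavior") that any single p below 0.05 would count as success. No such rule is written. The word joining the two behaviors can equally be read as matching each intervention to its own target.

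**Conclusion.** The plan is wrong as written, within a limited scope. The level in the analysis section does not match the level at which the trial was sized. Taken literally, it gives a familywise error per outcome of about 9% (two contrasts with control) or 12% (three pairwise), against 3.1% or 4.4% at 0.017. These figures assume equal arms, no true differences, approximately normal test statistics, and clustered models that hold their nominal level for each single test.

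It would be going too far to say that the sample size already pays for 0.017. On the sponsor's own figures, 110 per arm covers sedentary time (101) and Stroop (102), but falls short for guideline attainment (125) and stress (134). The power figures rest on the reversed inflation steps, which are an assumption. The shortfall is a reason to state the power honestly. It does not by itself justify the looser threshold.

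**What to change.** In Statistical analyses, state that 5% two-sided is the familywise level across the group comparisons for each sized outcome. Say that each comparison is tested at 0.017, or that Holm's procedure is used, and say whether the comparison between the two interventions belongs to the family. This brings the section into line with Sample size.

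Apply the rule to participants as randomized. The same section attaches the name intention to treat to a set defined by attending three or more of the five counselling sessions. The waiting list has not started its intervention by the 6-month measurement, so that set cannot serve as the basis for the comparison with control.

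If multiplicity across outcomes is to be controlled too, say so as a separate decision. The division by three does not provide it.

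The cost is a change of wording and some results with p between 0.017 and 0.05 that could no longer be called significant. The protocol should also restate power at 110 per arm under the corrected level: about 84% for sedentary time and for Stroop, 73% for guideline attainment and 69% for stress, with the inflation formula written out.

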### Randomization

In order to control contamination and to limit interaction between the different groups, randomisation will be done on a cluster level. We aim to have 24 clusters (8 clusters per arm), 10 at Intrum and 14 at ICA-gruppen. Clusters will be composed while considering: 1) having a team or line manager, 2) having regular group meetings, 3) limited regular meetings with other teams. Block randomisation and assignment will be performed using a computer-generated random number list. Groups will be randomly allocated (1:1) with stratification for company and cluster size (large vs small). In order to implement the interventions in an order consistent with logistical capacity matched randomization will be used in case needed. Randomization will be performed after finishing first data collection and participants will be notified by email. Randomization and allocation will be performed by researchers not involved in data collection. Research assistants involved in data collection and processing will be blinded for group allocation.

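### The sample sizes assume a per-comparison level of 0.05/3 = 0.017, but the analysis section tests at 5% and carries no correction over, so type I error across the arms is not held at 5%.

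*Protocol article*

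**What the plan says.** The protocol article fixes a significance level in two places.

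- **Sample size:** the calculation is made "with a power of 80% and significance level of 0.05, corrected for 3 groups (0.05/3 = 0.017". This applies to all four sized outcomes: meeting the activity guidelines, sitting time, stress and the Stroop test. The sizes after all three steps are 125, 101, 134 and 102 per group.
- **Statistical analyses:** "Statistical significance will be set at the 5% level (two-tailed". The sentence covers proximal, distal and secondary outcomes alike. On the comparisons, the section says "The models will include allocated group (reference group = control group) and baseline values".

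The Design section describes three arms with a waiting list control. The primary hypothesis, under Research questions, compares the interventions with that control at 6 months. The 0.017 level appears only in the Sample size section. The recruitment target of 110 per arm (330 in total) is given in the abstract.

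**The concern.** The authors decided that three arms call for a stricter level and paid for it in sample size. The rule by which results will be called significant does not mention it. A contrast with p between 0.017 and 0.05 would be positive under the Statistical analyses section and negative at the level for which the trial was sized. If 5% is applied to each model coefficient, which is how the sentence will normally be read, false positives across the arms are not held at 5%. The stated 80% power also belongs to a test that the analysis section does not describe.

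**Working it through.** **Inputs (Sample size section).** Power 80%. Activity 30% v 60%; sitting difference 1 h/day, SD 1.4; stress 26% v 5%; Stroop difference 7 s, SD 9.85. Proportion of variance between clusters 0.05; cluster size mean 14, SD 5.83. Loss: 3 clusters of 14 (taken as one per arm) and 20% of participants.

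**Step 1: which level was used?** For a two-sided test, n = (z(1−α/2) + z(0.80))² × v. For proportions (unpooled) v = (p1q1 + p2q2)/d²; for means v = 2(SD/difference)².

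- Activity: v = (0.21 + 0.24)/0.09 = 5.000
- Sitting: v = 2 × 1.4² = 3.920
- Stress: v = (0.1924 + 0.0475)/0.0441 = 5.440
- Stroop: v = 2 × (9.85/7)² = 3.960

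The multiplier (z + z)² is 10.422 at 0.017, 9.505 at 0.025 and 7.849 at 0.05.

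The design effect is 1 + [(CV² + 1) × 14 − 1] × 0.05 with CV = 5.83/14, which gives 1.771 (printed 1.77). The printed final sizes follow from n × 1.77 × 1.2 + 14.

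| Level | First step (activity / sitting / stress / Stroop) | Final size per arm |
|---|---|---|
| printed | 52 / 41 / 57 / 41 | 125 / 101 / 134 / 102 |
| 0.017 | 52.1 / 40.9 / 56.7 / 41.3 | 124.7 / 100.8 / 134.4 / 101.7 |
| 0.025 | 47.5 / 37.3 / 51.7 / 37.6 | 115 / 93 / 124 / 94 |
| 0.05 | 39.2 / 30.8 / 42.7 / 31.1 | 97 / 79 / 105 / 80 |

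The 0.017 row matches every printed figure on rounding, and the 0.05 row matches none. The sizing did use 0.017.

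**Step 2: false positives per outcome.** Assume equal arms, one shared control, no true effects, and tests that hold their nominal level. With c = z(1−α/2), the two contrasts with control have correlation 0.5. The chance of at least one rejection is 1 − ∫φ(x)[Φ(x + c√2) − Φ(x − c√2)]² dx. For all three pairwise contrasts it is the upper tail of the studentized range for three groups at c√2.

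| Level per contrast | Two contrasts with control | Three pairwise contrasts |
|---|---|---|
| 0.05 | 9.1% | 12.2% |
| 0.025 | 4.6% | 6.4% |
| 0.05/3 | 3.1% | 4.4% |

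**Step 3: power at the printed sizes if tested at 5%.** Power = Φ(√(n/v) − 1.960) with the first-step n. Activity: Φ(√(52/5.000) − 1.960) = Φ(1.265) = 0.90. Sitting, stress and Stroop also give 0.90.

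**Step 4: power at 110 per arm.** Reversing the plan's last two steps, (110 − 14)/1.2 = 80 and 80/1.77 = 45.2 effective participants per arm.

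| Level | Activity | Stress |
|---|---|---|
| 0.05 | 85% | 82% |
| 0.025 | 78% | 74% |
| 0.017 | 73% | 69% |

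Sitting and Stroop stay above 80% at all three levels.

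**The case against.** The best defence is that both sections mean the same overall 5%. The Sample size section itself starts from 0.05 and then divides it, and the analysis section never says that 5% is uncorrected. The article is condensed, and a multiplicity procedure is often left to the analysis plan. That reading is possible. But the analysis section states a level and names neither a family of contrasts nor a procedure, so a reader would apply 5% to each coefficient. This is a mismatch between two stated rules, not a missing detail.

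Three stronger readings are tempting and are not supported:

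- **That the plan can have its power or its error control, but not both.** At the printed sizes, a 0.017 test gives 80% power and holds the error below 5%. The conflict arises only at 110 per arm, which is a separate shortfall against the printed 125 and 134.
- **That the mismatch leaves the trial short of power.** Testing at 5% raises power at the printed sizes to about 90%.
- **That dividing by 3 is an error.** Control as reference gives two contrasts, and the primary hypothesis names only those. But the analysis section asks whether the groups differ, and the Background asks which behavior has the greater impact, so a contrast between the active arms is plausible. If it is not intended, 0.05/3 is merely conservative.

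One point of context stands. Each intervention targets its own proximal behavior, so for activity and for sitting one of the two contrasts is off-target. The 9.1% describes the shared distal outcomes better.

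**Conclusion.** The point holds as a mismatch in the significance level. The trial is sized at 0.017 per comparison and, as written, tested at 5%. Per outcome, the chance of at least one false positive is about 9.1% over two contrasts or 12.2% over three, where the sizing level would give 3.1% or 4.4%. The consequence is loss of type I error control across arms. These figures assume equal arms sharing one control and a 5% level applied to each contrast; they cover the arms only, not the number of outcomes. The shortfall of 110 per arm for activity and stress is a related but separate matter.

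**What to change.** In the Statistical analyses section, name the confirmatory contrasts for the main outcomes and test each at the level used for sizing: two-sided 0.05/3 with matching confidence intervals, or a family-wise 5% procedure such as Holm over the same contrasts. The printed sizes then stand, and the change is about one sentence.

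If only the two contrasts with control are confirmatory, 0.05/2 in both sections is an acceptable alternative. By the plan's own steps the sizes become 115, 93, 124 and 94. It would not suffice for three confirmatory contrasts (6.4% in the table above). These sizes keep the plan's multiplication by 1.2 for 20% loss; dividing by 0.8 would ask for a few more (activity: 84.1/0.8 + 14 = 119).

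The cost is that a main-outcome contrast with p between the corrected level and 0.05 can no longer be claimed.

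Neither option closes the recruitment gap. The plan should state that 110 per arm is below the required size for activity and stress at either corrected level, with power of about 73% and 69% at 0.017, or 78% and 74% at 0.025.

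### None of the crude, adjusted, per-protocol and intention-to-treat versions is named as decisive, and convention cannot choose because intention to treat is itself defined by session attendance

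*Protocol article*

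**What the plan says.** The Statistical analyses section of the protocol article makes four statements that matter here.

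- Models: "Both crude models and models adjusted for potential confounders will be determined". Both are multilevel models that account for company and clustering, and "The models will include allocated group (reference group = control group) and baseline values".
- Analysis sets: "All analyses will be performed using both per protocol and intention to treat approaches".
- Definition of one set: "intention to treat is defined as persons attending at least 3 out of 5 counselling sessions". No separate definition of per protocol is given.
- Significance: "Statistical significance will be set at the 5% level (two-tailed"), with no distinction between versions.

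The Research questions section begins the main hypothesis with "The primary hypothesis is that the multi-component interventions will favorably change office-workers physical activity or sedentary behavior" and fixes the comparator (waiting list) and the time point (6 months). It names neither a model nor an analysis set. The one restraint on the adjusted model is "Potential confounders will be defined a priori based on the findings from the larger research project".

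**The concern.** Two models on two sets give four estimates and four p-values for the same arm, outcome and time point. If they disagree, for example p = 0.03 in the adjusted per-protocol version and p = 0.09 in the crude intention-to-treat version, the document does not say which one answers the primary hypothesis.

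Normally this would be a small matter: a reader would take intention to treat as leading and the rest as supportive. That default is not available, because the set labelled intention to treat is selected on attendance. Two things are then at stake. One is the false-positive rate of a single contrast, if more than one version may support the claim. The other is bias: people who come to counselling sessions may differ from those who do not, so a difference seen in an attendance-selected set may reflect who attends and not what the intervention does.

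**Working it through.** **1. Is there a randomised comparison among the stated versions?** The intention-to-treat set requires attendance at 3 of 5 sessions. The Waiting list section says controls are passive until the 6-month measurement and start their intervention afterwards. At 6 months no control can have met the criterion. Read literally, the set contains no controls. Read charitably, it compares attenders in the active arms with all controls, which is a per-protocol comparison. On neither reading are all randomised participants analysed as allocated. Per protocol is undefined, so it does not supply that analysis either.

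**2. How many versions?** 2 models × 2 sets = 4 per contrast and outcome. If the two sets turned out to be the same people, 2 versions would remain (crude and adjusted), both attendance-selected.

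**3. False-positive rate if any version may count.** The document gives no figure for this, so there is nothing to reproduce. The inputs are assumptions, because neither the variance explained by the confounders nor expected attendance is stated:

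- R² = variance explained by the extra confounders beyond baseline value: 3% to 30%.
- a = share of the active arm in the attendance-based set: 60% to 90%.
- One set is taken as all randomised and the other as attenders against all controls. Attendance is unrelated to outcome, arms are equal in size, and clustering is ignored.

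Under no effect, the correlations of the test statistics are:

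- crude with adjusted: √(1 − R²), from √0.97 = 0.985 to √0.70 = 0.837;
- full set with attenders: √(2a/(1 + a)), from √(1.8/1.9) = 0.973 to √(1.2/1.6) = 0.866;
- pairs that differ in both respects: the product of the two.

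The probability that at least one of four |z| exceeds 1.96 (2 million draws per cell):

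| R² | a = 90% | a = 80% | a = 60% | crude or adjusted only |
|---|---|---|---|---|
| 3% | 7.0% | 7.6% | 8.5% | 5.8% |
| 10% | 7.8% | 8.5% | 9.4% | 6.5% |
| 30% | 9.1% | 9.8% | 11.0% | 7.6% |

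A person-level simulation (80 per arm, least squares with t-tests, 20,000 trials per setting) gave 7.0% at R² = 3%, a = 90% and 11.4% at R² = 30%, a = 60%. A single version gave 5.0% and 5.2%. Allowing for simulation error and the approximations, I state the range as roughly 7 to 12%.

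**4. Bounds.** Four independent tests would give 1 − 0.95⁴ = 18.5%. That does not apply, because the versions share most of their data. Correlations of 0.7 for both choices give 13.7%, but they imply R² = 1 − 0.49 = 51% and a = 0.49/1.51 = 32%, outside the range taken here.

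**5. With one version decisive.** The rate per contrast returns to 5%.

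**The case against.** The strongest reply is that a condensed article has merely not said which analysis leads, and that an analysis plan not shown may do so. Planning all four versions is normal practice. That stands as far as it goes: silence on ranking alone would not be a finding. What remains is that the article does state a definition of intention to treat, and that definition removes the analysis to which a reader would default.

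A reader might infer that the plan lets a positive result rest on whichever version reaches significance. The document does not support this. It says that the versions will be produced; it nowhere calls them equal or says that any of them may carry the claim. The 7 to 12% is therefore conditional.

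A reader might also infer that the crude model is an unadjusted comparison, which would make the crude-versus-adjusted choice a large one. It is not: baseline value, company and clustering are already in the models, and the extra confounders are to be fixed beforehand. That choice alone gives 5.8 to 7.6% in the table. Fixing confounders in advance does not, however, settle which of the two models decides.

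It is fair, too, that the count of four depends on a difference between the two sets that the document does not spell out. If the sets coincide, the inflation is smaller, but no randomised comparison is left at all.

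**Conclusion.** The concern holds in this form: the protocol names no decisive version for its primary hypothesis, and its definition of intention to treat prevents convention from supplying one. The effect on the error rate is modest, about 1.4 to 2.4 times the nominal 5% (7/5 to 12/5). It arises only if more than one version may support the claim. It rests on the assumed confounder variance and attendance, on attendance unrelated to outcome, and on independent persons.

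The more serious part cannot be sized from the document: every stated version may be selected on attendance, and any link between attendance and outcome then enters the estimate as bias. The point should be corrected before the analysis. It is not evidence that results will be reported selectively.

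**What to change.** In the Statistical analyses section:

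1. Replace the attendance-based definition. Intention to treat means all randomised eligible participants, analysed in the arm to which their cluster was allocated. Keep the exclusion of very active persons from the In- and exclusion criteria section, applied identically to all arms from baseline accelerometer data. The Randomization section places randomisation after the first data collection, so this exclusion need not depend on allocation.
2. Call the set with at least 3 of 5 sessions per protocol, and state how waiting-list participants enter it, since they have no sessions before 6 months.
3. State that the primary hypothesis is decided only by one multilevel model on the intention-to-treat set, with baseline value, the randomisation strata (company and cluster size) and the covariates fixed in advance. Letting the simpler baseline-adjusted model lead would also restore a single answer; what matters is that one is named before the analysis.
4. State that all other versions are sensitivity analyses and cannot replace or overturn the decisive one.

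The cost is a few sentences, and all planned versions can still be run. The downside is that a positive result found only in a sensitivity version can no longer support the claim.
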